### Risk Management Protocol

Psychologists will monitor participant responses and distress levels throughout the intervention. Although direct contact with participants will not occur during the standard course of the trial, a psychologist or psychiatrist will contact participants by email and/or telephone in certain circumstances, as outlined below. After each writing session, participants will be required to rate how distressing the writing session was on a 6-point scale. If participants indicate that a writing session was at all distressing (by responding 1 or greater), then the *Writing for Health* program will automatically display a feedback page outlining strategies to manage distress and suggest that they contact their GP if further support is needed. This page also includes the telephone number of a 24-hour telephone mental health helpline available in Australia (Lifeline). If the participant responds with a distress rating of 5 or 6 after any writing session, they will also be emailed by a psychologist, with further telephone contact based on the clinical discretion of study psychologists and psychiatrist.

Participants’ depression and anxiety scores on the Patient Health Questionnaire-9 (PHQ-9) and Generalized Anxiety Disorder-7 (GAD-7), respectively, will also be monitored. If a participant’s score is in the severe range for depression or anxiety at one-month or three-month follow-up and/or the participant indicates possible suicidal thoughts by responding 1 or greater on item 9 of the PHQ-9 (“Over the past two weeks, have you been bothered by… thoughts that you would be better off dead, or of hurting yourself in some way?”), the participant will be emailed and then telephoned by a *Writing for Health* psychologist to assess the supports the participant is receiving, and provide contact details or referrals to appropriate services. In addition, the *Writing for Health* program will provide automatic feedback pages at the end of the follow-up questionnaire sessions for participants who have scored in the above ranges, providing information on how to access mental health support, including the recommendation to contact their GP and the telephone number for Lifeline. Similarly, at the final three-month follow-up, the same procedure will apply to participants who score in the moderate or greater range for depression or anxiety on the PHQ-9 or GAD-7, respectively.

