### Participants

#### Recruitment

Participants will be recruited online from Australian diabetes-related websites and publications, and from advertisements in waiting rooms of diabetes services and general practitioners (GPs) throughout Australia. Participants will apply for the study via the *Writing for Health* website [66], where they will complete an automated screening questionnaire (which also provides baseline data) after reading the study information and provide informed consent. Excluded applicants will immediately receive an onscreen message that informs them that the program is not suitable for them, and will provide links to appropriate resources. All potential participants will be provided with feedback on the severity of their depression and anxiety symptoms. Participants who meet eligibility criteria will proceed to online registration with the program, complete further online questionnaires (for further baseline data), be automatically randomized, and then complete the first writing session.

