### Procedure

Potential participants will visit the *Writing for Health* website [66], read the participant information, and indicate their consent to participate by checking a box. Potential participants will complete screening questionnaires with automated feedback, and if eligible, can then register to participate. Following completion of further online questionnaires, participants will be automatically randomized to one of two conditions: iBFW or control writing. Participants can then proceed to the first session of their 3-day writing intervention (either iBFW or control writing). Immediately before and after each of their three 15-minute writing sessions, participants will be asked to rate their current mood. In addition, following each writing session, participants will be asked to rate how personal, meaningful, and distressing their writing session was that day, and can comment on the writing session if they wish. At the completion of their three-day writing intervention, participants will be asked to complete the online *Feedback Questionnaire*, to assess user satisfaction and perceived helpfulness. Outcome measures will be administered in the online *One-Month* and *Three-Month Follow-Up Questionnaires* (in addition to baseline).

Participants will be sent automatic reminder emails by *Writing for Health* on day 2 and day 3 of their writing intervention, and also one-month and three-months postintervention, prompting participants to complete their follow-up questionnaires. All participants will be provided with automatic feedback of the range in which they scored on depression and anxiety measures, at baseline, one-month, and three-month follow-ups.

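### The automatic support page for suicidal thoughts (PHQ-9 item 9) is placed at the follow-up sessions, although the same answer can be given at screening by someone who is then randomised and starts writing

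*Protocol article*

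**What the plan says.** The Risk Management Protocol section of the protocol article sets two responses for participants whose PHQ-9 or GAD-7 answers raise concern.

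- **Psychologist contact.** An email and then a telephone call follow if the score is in the severe range at one or three months and/or if "the participant indicates possible suicidal thoughts by responding 1 or greater on item 9 of the PHQ-9".
- **Automatic page.** The program also provides "automatic feedback pages at the end of the follow-up questionnaire sessions for participants who have scored in the above ranges". The page explains how to reach mental health support, advises seeing the GP and gives the Lifeline number.

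The PHQ-9 is not confined to follow-up. Table 1 lists it at baseline, one month and three months. The Eligibility textbox uses it for exclusion (total above 10, or GAD-7 above 8), and the Recruitment section says that screening also supplies baseline data. No criterion refers to item 9.

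The feedback described at entry concerns severity. Recruitment says: "All potential participants will be provided with feedback on the severity of their depression and anxiety symptoms". Procedure promises "automatic feedback of the range in which they scored on depression and anxiety measures, at baseline, one-month, and three-month follow-ups". Links to resources are described for applicants who are excluded. For those who are eligible, registration, further questionnaires and automatic randomisation follow, and then: "Participants can then proceed to the first session of their 3-day writing intervention".

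**The concern.** The protocol sets its own threshold for concern on item 9 and collects that item before anyone is randomised. The immediate, automatic part of its response is nevertheless placed at sessions held a month or more after the writing. Someone who reports suicidal thoughts at screening but has a low total passes the eligibility rule. The only feedback stated for that person is a severity range, which may sit in the lowest band, and the next step is a writing exercise.

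The stake is participant safety, not any estimate or test. An applicant turned away for an unrelated reason is stated to receive resource links at once. An eligible entrant who has just met the suicidality threshold is not.

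**Working it through.** The article gives no figure of its own to reproduce here. The check is a scoring bound plus a comparison of sections.

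**Inputs**
- PHQ-9: nine items, total 0 to 27 (Depression Symptoms), so each item scores 0 to 27/9 = 3.
- Eligible if the total is 10 or less (Eligibility textbox, which excludes totals above 10).
- Below mild if the total is 4 or less (Depression Symptoms, first cut-off 5).
- Item-9 trigger: 1 or more (Risk Management Protocol).

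**Can an item-9-positive applicant be eligible?** With item 9 equal to *k*, the other eight items may sum to at most 10 − *k* for eligibility, and to at most 4 − *k* for a range below mild.

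| Item 9 | Other eight items, still eligible | Other eight items, still below mild |
|---|---|---|
| 1 | 10 − 1 = 9 | 4 − 1 = 3 |
| 2 | 10 − 2 = 8 | 4 − 2 = 2 |
| 3 | 10 − 3 = 7 | 4 − 3 = 1 |

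Every positive answer is compatible with entry, and with the lowest feedback range. Enumerating all response patterns agrees. Of 49,313 patterns with a total of 10 or less, 14,266 + 8,938 + 5,115 = 28,319 have item 9 at 1 or more. This counts possible patterns and is not a prevalence. It shows only that the total-score rule does not remove such applicants. The GAD-7 limit of 8 does not involve item 9.

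**What does that person meet, and when?**
1. *At screening:* severity-range feedback. No item-9 content is stated.
2. *Before session 1:* automatic randomisation, with no clinician step described.
3. *After each session:* a GP and Lifeline page, but only if the writing session is rated 1 or more for distress. That rating concerns the writing, not the item-9 answer. An entrant who finds the writing not at all distressing is not stated to see the page.
4. *At one month:* the first session at which the item-9 page is stated to appear, after all three writing sessions.

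**Does the one-month answer make up for the missing page?** Item 9 begins "Over the past two weeks, have you been bothered by", so it covers two weeks. Asked one month after the intervention, it does not reach back to entry. A person who answers 0 by then, or who has left the study, would not see the item-9 page.

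**Does the contact clause cover baseline?** The words naming the one- and three-month follow-ups are attached to the severe-score condition. The item-9 condition after the and/or has no time point. It can be read as applying at every PHQ-9 administration, or as sharing the follow-up timing of the clause before it.

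**The case against.** The strongest reply is that the more important safeguard probably covers baseline already. Entrants cannot be in the severe range at entry (PHQ-9 severe starts at 20 and GAD-7 severe at 15, against entry limits of 10 and 8). It therefore makes sense to tie the severe-score condition to follow-up and leave item 9 untimed. On that reading a baseline answer brings a psychologist's email and call, and only a supplementary page is missing. This largely stands. What it leaves open is that the wording permits the other reading, and that nothing says the contact comes before session 1.

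The second reply is that this is a condensed article. The full risk management protocol is not shown, and screening is said to come with automated feedback. This stands in part, since the full document may say more. But the article does state the timing of the page, and Procedure names baseline explicitly where baseline is meant.

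Third, other protection runs early: psychologists monitor responses throughout the intervention, the session-distress page can appear from day 1, and usual care continues. All true, but neither the monitoring nor the distress page is stated as a response to a baseline item-9 answer.

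Three stronger readings are tempting and are not supported:
- *That nothing responds to a positive baseline answer.* The contact clause may well do so.
- *That item 9 is the only score trigger an entrant could meet.* A PHQ-9 total of 10 is both eligible and in the moderate range, which is itself a trigger, although the section applies it only at three months.
- *That the expected attrition of up to 50% measures the size of the gap.* It is general attrition and says nothing about how many entrants score 1 or more on item 9.

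**Conclusion.** The point holds in a limited form. As the Risk Management Protocol section is worded, the automatic item-9 page belongs to the follow-up sessions. An entrant with item 9 at 1, 2 or 3 can be eligible, even with a total of 4 or less, and can be randomised and start session 1 with only severity-range feedback stated. Whether psychologist contact covers that entrant is ambiguous, and its timing relative to session 1 is not given.

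The number of people affected cannot be derived from the article. The conclusion rests on the natural reading of the sentence that places the page at follow-up, and on the full risk management protocol not adding a baseline page. No statistical result depends on it. Because it concerns a suicide-risk threshold the protocol itself set, and the remedy is cheap, the change should be made. Confidence is medium, given the unseen full document.

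**What to change.** Amend the Risk Management Protocol section in two places.

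1. Show the existing support page (GP advice, Lifeline) immediately after any PHQ-9 administration with item 9 at 1 or more, including screening/baseline. At entry it should come before randomisation, so that it is identical in both arms.
2. State that the existing psychologist email and telephone contact for item 9 at 1 or more applies at baseline as well as at one and three months.

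No new exclusion criterion is needed, no new data are collected and no analysis changes.

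The cost is low but not nil. It takes one conditional page in the live screening flow, reusing content already built for follow-up. It also needs a minor ethics amendment, because the protocol is approved and data collection is under way. There may be a few extra psychologist contacts at entry if the contact rule has been read as follow-up only. Only people screened after the change would benefit.

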### Randomization

Randomization to the two groups will be automatically generated by the *Writing for Health* content management system after participants have registered with the program. Randomization is therefore concealed to the researchers.

### Primary Outcome Measures

#### Diabetes Distress

The Diabetes Distress Scale (DDS17) [67] is a 17-item self-report measure of psychosocial stress associated with diabetes, with four reliable subscales: emotional burden (feeling overwhelmed by diabetes), physician-related distress (worries about access, trust, care), regime-related distress (concerns about diet, physical activity, medications), and interpersonal distress (not receiving understanding and appropriate support from others). Cut-off points on the DDS17 have been established for little or no distress, moderate distress, and high distress [68].

#### Benefit-Finding

The 17-item Benefit Finding Scale [51] was developed to investigate benefit-finding in women with early stage breast cancer. In the current study, the stem question is modified from, “Having had breast cancer has…” to, “Having had diabetes has…” Participants are asked to respond to each of the 17 perceived benefits, such as, “has lead me to be more accepting of things” and, “has brought my family closer together” on a five-point scale with labels of *not at all* (1), *a little* (2), *moderately* (3), *quite a bit* (4), and *extremely* (5). This scale has previously been adapted for use in diabetes (with one item removed) and found to have one large factor and good internal consistency (Cronbach alpha=.89) in a population of adolescents with type 1 diabetes [55]. Table 1 provides an overview of all measurement tools and administration time-points.

**Table 1 table1:** Measurement tools and questions at each time-point.

		Questionnaires	Baseline	Pre-writing session	Post-writing session	Post-final session	1-month follow-up	3-month follow-up
**Demographics**			✓					
**Primary outcomes**								
	Diabetes distress	Diabetes Distress Scale	✓				✓	✓
	Benefit finding	Benefit Finding Scale	✓				✓	✓
**Secondary outcomes**								
	Depression	Patient Health Questionnaire-9	✓				✓	✓
	Anxiety	Generalized Anxiety Disorder-7	✓				✓	✓
	Diabetes self-care	Summary of Diabetes Self-Care Activities Measure (Revised)	✓				✓	✓
	Self-rated health	Single item	✓				✓	✓
	Health care utilization	Single item	✓				✓	✓
	Positive and negative affect	International Positive and Negative Affect Schedule Short Form		✓	✓			
	Experiences during writing session	Questions assessing how personal, meaningful, and distressing the writing session was			✓			
	User satisfaction	Feedback Questionnaire				✓		

### Secondary Outcome Measures

#### Depression Symptoms

The PHQ-9 [69] is a brief, widely used, reliable, and valid 9-item self-report that measures both the severity of depression over the preceding two weeks and diagnosis of depression based on criteria of the Diagnostic and Statistical Manual of Mental Disorders, 4^th^Edition (DSM-IV). This questionnaire has established cut-off scores of 5, 10, 15, and 20, representing *mild*, *moderate*, *moderately severe*, and *severe* depression. The total score ranges between 0 and 27, with scores equal or above 10 having a sensitivity of 88% and a specificity of 88% for major depression [69].

#### Anxiety Symptoms

The GAD-7 [70] is a brief, widely used, reliable, and valid 7-item self-report that measures the severity of anxiety. Scores on the GAD-7 range from 0 to 21; scores of 5, 10, and 15 represent *mild*, *moderate,* and *severe* anxiety symptoms. A total score of 8 on the GAD-7 has been identified as an important threshold for identifying the presence of an anxiety disorder [71].

#### Positive and Negative Affect

The International Positive and Negative Affect Schedule Short Form (I-PANAS-SF) [72] is a reliable and valid 10-item measure of positive and negative affect, which is comprised of 10 words that represent positive and negative affect. The correlations that this scale has with the positive and negative affect scales of the full 20-item form of the Positive and Negative Affect Schedule (PANAS) are .92 and .95, respectively [72]. Instructions were modified to assess state rather than trait affect, using the instructions of the 20-item PANAS-Immediate Version [73]. Participants will be instructed to indicate the degree of specific affect they feel, “right now, at the present moment”, on a scale of 1 to 5 (1=very slightly/not at all; 5=extremely).

#### Diabetes Self-Care

The Summary of Diabetes Self-Care Activities Measure (Revised) [74] is an 11-item self-report measure of self-care of diabetes mellitus (including diet, exercise, blood sugar testing, foot care, and smoking) that is widely used both clinically and in research. Items in the revised version were selected based on their psychometric properties, sensitivity to change, and ease of scoring and interpretation [74]. In a critical appraisal of 26 different measures of diabetes outcomes, the Summary of Diabetes Self-Care Activities Measure (Revised) was one of only three measures to meet all criteria of suitability, validity, reliability, and sensitivity to change [75].

#### Self-Rated Health

Self-rated health will be assessed by the question, “In general, how would you rate your health at present?” The five response options are *very good*, *good*, *fair*, *poor,* and *very poor*. Responses to this question have previously been found to be significantly associated with blood glucose indicator hemoglobin A1c (HbA1c; with poorer self-rated health associated with higher HbA1c levels) and number of self-reported diabetes-related symptoms in patients with type 2 diabetes [76].

#### Health Care Utilization

Participants will be asked to answer the question, “In the past month, how many times have you visited a doctor or other health care professional?” This same question will be administered at three time-points: baseline, one-month follow-up, and three-month follow-up.

### Additional Measurements

We will collect sociodemographic information (age, gender, education, and occupation), diabetes-related information (type, duration of illness, management, and complications), and participant feedback about the program.

#### Experiences During Writing Session

Immediately after each writing session, participants will be asked to rate how meaningful, personal, and distressing their writing exercise was, on a 7-point scale (0=not at all; 6=extremely). Similar questions have been used as manipulation checks in previous studies of therapeutic writing [42,77]. In addition, participants in the iBFW intervention condition will be asked immediately after each writing session if they were able to identify *any* positive thoughts or feelings about living with diabetes in their writing session.

#### Feedback Questionnaire

A 12-item self-report questionnaire was developed to assess participants’ experiences and perceptions of the *Writing for Health* program. Item content was informed by self-report measures from other evaluations of Internet-based interventions. Items 1 to 6 ask participants to rate responses on a 5-point scale (from *not at all* to *very*) regarding aspects of usability and perceived helpfulness of the *Writing for Health* program, including how easy to use it was. Items 1 to 3 are taken from the Internet Intervention Evaluation Questionnaire [78]. Items 4 and 5 are modified from items previously used to assess credibility of writing interventions (asking participants to rate how logical the writing exercises seemed and how confident they would be in recommending it to a friend) [79]. Item 6 examined the perceived helpfulness of the writing exercises in reducing stress. Item 7 examined technical difficulties with the online program, and items 8-12 were open-ended questions examining the most helpful and least helpful aspects of the program, and any suggested improvements.

### Statistical Analyses

Statistical analyses will be conducted using SPSS 22 software. Group differences in demographic data, diabetes-related variables, and baseline measures will be analyzed using one-way analysis of variance (continuous variables) and chi-square tests (categorical variables). Similar analyses will be conducted to compare participants who do (nondropouts) and do not (dropouts) complete all questionnaires at each of the time-points, to explore possible biases in study attrition. Analyses will be conducted to validate the writing intervention instructions in several ways:

To examine immediate emotional responses to the writing interventions, scores on the I-PANAS-SF [72] administered immediately before and after each writing session will be analyzed using a 2 (group) x 3 (session) x 2 (positive affect and negative affect) repeated measures multivariate analysis of variance. This test will be used to investigate the hypothesis that the benefit-finding group will have greater increases in positive affect postwriting, relative to the control group.

The content of the written scripts in both groups will be assessed using the Linguistic Inquiry Word Count 2007 software program [82], to examine differences in positive emotion words and cognitive insight words. This validated method provides a content analysis of the language used in the scripts, and quantifies the number of words used from specific categories (eg, emotions, cognitive processes). This approach will be used to investigate the hypothesis that the benefit-finding group will use more positive emotion words and more cognitive insight words than the control group.

Scores on the feedback questionnaire, a measure developed to assess user satisfaction and perceived usefulness of the intervention, will be compared between the two groups using analyses of variances. These tests will be used to examine the hypothesis that the participants in the benefit-finding group will have higher levels of user satisfaction and perceived helpfulness of the writing tasks, relative to the control group.

Outcome data at the one-month and three-month follow-up time-points will be analyzed on an intention-to-treat basis using linear mixed modelling, with time-points as a within-group factor and intervention as a between-group factor. The interaction of time and study condition will be examined in each analysis, as a significant interaction will indicate a group difference in the pattern of change over time in the outcome of interest. Significant interactions will be explored using Bonferroni adjusted comparisons of the two groups at one-month and three-month follow-ups. All effects will be tested at *P*<.05. Within-group and between-group Cohen *d* effect sizes will be calculated.

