### Study Aims and Hypotheses

The primary outcomes of this RCT will be the impact of the iBFW, compared to a control writing condition, on diabetes distress and benefit-finding in diabetes. Our primary hypotheses are that adults with type 1 or type 2 diabetes randomized to receive iBFW will demonstrate significantly reduced diabetes distress and significantly increased benefit-finding for diabetes, compared to the control condition, at both one-month and three-month follow-ups.

Secondary outcomes will include symptoms of depression, symptoms of anxiety, diabetes self-care, health care utilization, and perceived self-health. Our secondary hypotheses are that compared to those in the control condition, the iBFW group will demonstrate significant: (1) reductions in depression symptoms; (2) reductions in anxiety symptoms; (3) increased diabetes self-care; (4) reduced number of visits to health professionals; and (5) improved perceived health, at both one-month and three-month follow-ups.

This study also aims to examine validation of the intervention instructions by investigating immediate emotional responses to the writing tasks, and the number of positive emotion words and cognitive insight words used in the writing tasks. It is hypothesized that compared to those in the control condition, the iBFW group will (1) show greater increases in positive affect postwriting, and (2) use more positive emotion words and more cognitive insight words than the control group.

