## Methods

### Study Design

A 2 (conditions) x 3 (time) RCT design is planned. A flow diagram for the trial is shown in Figure 1. Participants will be randomized to either iBFW or an Internet-based control writing condition. Both conditions involve an intervention of 3 days of online writing. Outcomes will be assessed at 3 time points for both groups: baseline, one-month, and three-months postintervention. We will also assess self-rated current mood immediately prior to and following each writing session, and administer three survey questions (assessing how personal, meaningful, and distressing the writing exercise was) after each writing task. An online *Feedback Questionnaire* to assess user satisfaction and perceived helpfulness will also be administered postintervention.

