### Intervention and Control

#### Writing for Health

This RCT will be conducted using the online program *Writing for Health* [66], which was developed for this study by mental health researchers (including psychologists and a psychiatrist) at St. Vincent’s Hospital, Sydney, and the University of New South Wales. All stages of this study will be conducted online through *Writing for Health*, including information about the study, consent to participate, screening questionnaires with automated feedback, participant registration, randomization to one of two conditions, the writing intervention, and follow-up questionnaires. Automated reminder emails will be sent by *Writing for Health* to participants on each day of the intervention, and when it is time to complete their follow-up questionnaires.

*Writing for Health* provides minimal clinician assistance. Direct contact between participants and the clinicians will not occur in the standard course of the trial. Psychologists will monitor participant responses and distress levels throughout the intervention, and in accordance with the risk management protocol, will correspond with participants by email and phone to assess any support needed, and refer to appropriate services if required.

Participants registered with *Writing for Health* will be randomized to one of two conditions: iBFW or Internet-based use-of-time writing (control condition). Participants from both conditions will continue to receive usual care from their health services. Following randomization, both conditions involve participants writing online (in the *Writing for Health* program) for 15 minutes once a day, according to instructions provided. There will be three daily 15-minute online writing sessions (once per day for three consecutive days.) A timer on the screen counts down from 15 minutes, to allow participants to keep track of time during their writing session.

Information provided to participants in *Writing for Health* describes the aim of this study as investigating whether the writing exercises in the *Writing for Health* program improve the mental and physical wellbeing of people with diabetes. Participants will be informed that they will be randomized to one of two types of writing exercises, and both types of writing exercises will be described. However, research hypotheses will not be revealed.

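### As listed, the affect analysis has no before/after factor and no change score, so no term tests the hypothesised greater rise in positive affect

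*Protocol article*

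**What the plan says.** Under Study Design, the article plans to record "self-rated current mood immediately prior to and following each writing session", and the Writing for Health section gives three daily sessions. Each of the two affect scales is therefore scored on six occasions.

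Under Study Aims and Hypotheses, the iBFW group is expected to "show greater increases in positive affect postwriting" than the control group. The Statistical Analyses section enters the I-PANAS-SF scores from both occasions of every session and describes the model in these words: "using a 2 (group) x 3 (session) x 2 (positive affect and negative affect) repeated measures multivariate analysis of variance". It then ties the hypothesis to that analysis: "This test will be used to investigate the hypothesis that the benefit-finding group will have greater increases in positive affect postwriting".

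Nowhere does the article list a before/after factor for this analysis, define a post-minus-pre score, or use the pre-session score as a covariate.

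**The concern.** The hypothesis is about change within a session, compared between arms. A test of it needs a term that sets post-writing against pre-writing scores and asks whether that contrast differs by group. The three listed factors are group, session and affect type, and none of them separates the two occasions.

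The article relies on this analysis to show that the instructions did what they were meant to do. Immediate gain in positive affect is also the advantage that the Introduction and Discussion claim for benefit-finding writing over expressive writing. If the listed model is run literally, a real gain could go undetected. If the analyst repairs the model later, the choice of term may be made after the data have been seen.

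**Working it through.** **1. Count the layout.**
- Scores collected per participant: 2 affect scales x 3 sessions x 2 occasions = 12.
- Within-person cells in the listed design: 3 sessions x 2 affect types = 6.
- Ratio: 12 / 6 = 2. The factor left out has two levels, before and after.

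**2. Go through the terms of the listed design.**
- Group: whether average level differs between arms.
- Session: whether level differs across days.
- Affect type: whether positive and negative affect scores differ.
- Group x session: whether the difference between arms varies across days.
- Group x affect type: whether the gap between positive and negative affect differs between arms.
- Session x affect type, and the three-way term: how that gap varies over days, and whether that variation differs by arm.

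None of these is a post-versus-pre contrast.

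**3. Compare with the article's own follow-up analysis.** For the one-month and three-month outcomes, the same section makes time a factor and uses the time-by-condition interaction as the test of differential change. The affect analysis lacks the corresponding factor.

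**4. Illustrate what could be lost.** This step rests on assumptions that are not in the document: positive affect with SD 1 on every occasion, a common within-person correlation r = .6, all sessions complete, equal arms before writing, a 0.5 SD rise after writing in iBFW only, and two-sided alpha of .05. Group size is set at 26 per arm, the number the article's sample size section requires before its attrition allowance. The comparator is a group test on the mean of all six positive-affect scores. That is one way the listed model might be run, and the article does not specify it.

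*Pooled level*
- Difference in means = 0.5 / 2 = 0.25.
- Variance of the six-score mean = r + (1 - r)/6 = .6 + .4/6 = .667, so SD = .816.
- Standardised difference = 0.25 / .816 = .306.
- Noncentrality = .306 x sqrt(26/2) = 1.10 on 50 df.
- Power = 19%.

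*Change (mean post minus mean pre, equivalent to group x pre/post)*
- Difference = 0.5.
- Variance = 2(1 - r)/3 = .8/3 = .267, so SD = .516.
- Standardised difference = 0.5 / .516 = .968.
- Noncentrality = .968 x sqrt(13) = 3.49 on 50 df.
- Power = 93%.

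*Range over the assumed correlation and group size*

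| Per arm | r | Pooled level | Change |
|---|---|---|---|
| 26 | .4 | 24% | 80% |
| 26 | .6 | 19% | 93% |
| 26 | .8 | 16% | 99.8% |
| 52 | .4 | 43% | 98% |
| 52 | .6 | 34% | 99.8% |
| 52 | .8 | 28% | >99.9% |

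The layout count in steps 1 and 2 depends on none of these assumptions.

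**The case against.** The strongest reply is that the analysis is called multivariate, so positive and negative affect may be its two dependent variables and not a factor. If the values entered are post-minus-pre changes, the layout is group x session with two outcomes, and the group effect on positive-affect change tests the hypothesis. That analysis would be valid, and the stated aim of examining increases makes it a plausible intention. But the text speaks of scores, and no section defines a change score. Because the article lists the factors with their levels and assigns the hypothesis to that test, this is not detail left to a fuller document. What stands of the reply is that the failure belongs to the analysis as literally written, and not to every analysis the authors might have had in mind.

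A reader might infer three stronger points that the document does not support.

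- *The analysis would readily report a false gain from a difference present before writing.* Randomisation precedes session 1, so the expected pre-writing difference there is zero. A systematic gap before sessions 2 and 3 would have to come from earlier writing, which is itself an effect of allocation.
- *Up to half the participants would be dropped, against a promise of intention-to-treat analysis.* The attrition figure is not tied to the three writing days, and the intention-to-treat statement covers the one-month and three-month outcomes. It is true that a repeated measures MANOVA drops anyone with a missing session, but the article gives no rate for that.
- *The trial's main conclusions are at risk.* The article presents this analysis as validation of the instructions. Although Table 1 places affect among the secondary outcomes, the hypothesis is stated apart from the primary and secondary ones.

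**Conclusion.** The point holds for the text as written: 6 within-person cells are listed for 12 scores, and no term contrasts post with pre, so the named test does not answer the question assigned to it. This follows from the article's wording alone. The gap of about 19% against 93% is only an illustration, resting on an assumed correlation, effect, group size and pooled comparator. Across the ranges shown, the pooled-level test stays between 16% and 43% and the change test at about 80% or more.

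Severity is moderate. The primary outcomes, sample size and data collection are unaffected, and both occasions are already measured.

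**What to change.** Restate the analysis as group (2) x session (3) x pre/post (2), with positive affect and negative affect as separate dependent variables, and name group x pre/post on positive affect as the test of the hypothesis. Equivalently, analyse post-minus-pre change in positive affect by group and session and test the group effect.

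Fitting this as a linear mixed model with a participant random effect is an option that keeps participants who miss a session. Do not adjust for pre-session affect at sessions 2 and 3: those scores are measured after randomisation and may carry the effect of earlier writing.

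The cost is a sentence or two of text. No new data are needed. The article reports data collection as under way, so the change can be dated and recorded before the affect data are analysed.
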